## Abstract

**Background:**

Aging is associated with cognitive decline, increased risk for dementia, and deterioration of brain function. Modifiable lifestyle factors (e.g., exercise, meditation, and social interaction) have been proposed to benefit memory and brain function. However, previous studies have focused on a single exercise modality or a single lifestyle factor. Consequently, the effect of a more comprehensive exercise program that combines multiple exercise modalities and lifestyle factors, as well as examines potential mediators and moderators, on cognitive function and brain health in late middle-aged and older adults remains understudied. This study's primary aim is to examine the effect of a multi-domain exercise intervention on memory and brain function in cognitively healthy late middle-aged and older adults. In addition, we will examine whether apolipoprotein E (*ApoE*) genotypes, physical fitness (i.e., cardiovascular fitness, body composition, muscular fitness, flexibility, balance, and power), and brain-derived neurotrophic factor (BDNF) moderate and mediate the exercise intervention effects on memory and brain function.

**Methods:**

The Western-Eastern Brain Fitness Integration Training (WE-BFit) is a single-blinded, double-arm, 6-month randomized controlled trial. One hundred cognitively healthy adults, aged 45–70 years, with different risks for Alzheimer's disease (i.e., *ApoE* genotype) will be recruited and randomized into either a multi-domain exercise group or an online educational course control group. The exercise intervention consists of one 90-min on-site and several online sessions up to 60 min per week for 6 months. Working memory, episodic memory, physical fitness, and BDNF will be assessed before and after the 6-month intervention. The effects of the WE-BFit on memory and brain function will be described and analyzed. We will further examine how *ApoE* genotype and changes in physical fitness and BDNF affect the effects of the intervention.

**Discussion:**

WE-BFit is designed to improve memory and brain function using a multi-domain exercise intervention. The results will provide insight into the implementation of an exercise intervention with multiple domains to preserve memory and brain function in adults with genetic risk levels for Alzheimer's disease.

**Clinical trial registration:**

ClinicalTrials.gov, identifier: NCT05068271.

## Background

The rapid growth of the aged population has dramatically shifted the global demographic structure (United Nations., 2019). Advancing age has been associated with cognitive decline (Salthouse, 2019), progressive brain deterioration (Li et al., 2020), and increased incidence of various types of dementia, particularly Alzheimer's disease (AD) (Livingston et al., 2020). Considering the significant impact of age-related cognitive decline and AD on individual and societal levels (Roberts et al., 2015; Alzheimer's Association., 2021), as well as the limited curative effects of approved drugs on the progression of AD (Mehta et al., 2017), identifying potentially modifiable lifestyle factors for cost-effective, non-pharmaceutical preventative strategies has been a priority to lessen the adverse impact of aging on cognitive function and brain function.

### Exercise, memory, and brain function

Exercise, a planned, structured, and repetitive form of physical activity that aims to improve or maintain one or more components of physical fitness (e.g., cardiovascular and muscular fitness, balance, coordination, and power) (Caspersen et al., 1985), might be a promising non-pharmaceutical preventative approach for decelerating the trajectory of age-related cognitive decline (Chang et al., 2017b; Northey et al., 2018; Chen et al., 2020a) and the deterioration of brain function (Chen et al., 2020b), as well as for preventing or delaying the onset of AD (Valenzuela et al., 2020). Empirical research has revealed that exercise could beneficially alter the metabolomic profiles related to memory (Gaitán et al., 2021), and greater physical fitness levels associated with exercise have been linked to superior cognitive function (Netz, 2019) and to activation of the prefrontal cortex (Chen et al., 2019). Notably, epidemiological research has indicated that around 2% of dementia cases might be prevented by modifying the lifestyle of physical inactivity (Livingston et al., 2020), reflecting the beneficial role of non-pharmaceutical effects of exercise or higher physical fitness levels.

Exercise has been linked to improvements in working memory (Rathore and Lom, 2017; Chen et al., 2020a), which has been classically characterized as the capacity to dynamically store, update, and manipulate incoming information over short periods of time (Baddeley, 2012), and involves activation of cortical networks including the inferior frontal gyrus, anterior cingulate gyrus, hippocampus, and thalamus (Yin et al., 2013; Gutierrez-Garralda et al., 2014; Toepper et al., 2014). Additionally, deficits in working memory in particular accompany aging and AD (Kirova et al., 2015; Salthouse, 2019), and impaired working memory has been associated with increased psychological disorders (Chai et al., 2018). Fortunately, systematic reviews and meta-analyses have revealed that exercise training, such as aerobic exercise and resistance training, significantly improves working memory performance in cognitively healthy older adults and in older adults with mild cognitive impairment (MCI) (Northey et al., 2018; Chen et al., 2020a). Neuroimaging evidence has further described the beneficial effects of chronic exercise on brain function related to working memory in late middle-aged and older adults, reflected by greater activation in the prefrontal lobe, anterior circulate, and hippocampus (Chen et al., 2019), as well as attenuated aging effects on hippocampal volume (Erickson et al., 2011).

There are fewer studies that have examined the effects of exercise on episodic memory. Episodic memory is long-term, retrospective memory bound to temporal and spatial contexts (Tulving, 2002; Yonelinas et al., 2019) and has been closely linked to the hippocampus and surrounding medial temporal lobe structures (Yonelinas et al., 2019). Using direct (Hayes et al., 2016) or estimated (Boots et al., 2015; Freudenberger et al., 2016) measures of cardiovascular fitness, higher cardiovascular fitness levels have been linked to superior episodic memory in cognitively healthy older adults (Hayes et al., 2016) and late middle-aged adults at risk for AD (Boots et al., 2015). Similar findings have been reported in neuroimaging research. For instance, using the episodic associative learning task, a task that assesses hippocampal-dependent relational binding, Cole et al. (2020) indicated that healthy older adults with higher levels of cardiovascular fitness had larger hippocampal volumes and an enhanced rate of relational memory acquisition. Of note, the protective effects of cardiovascular fitness on episodic memory and brain health might be moderated by sex for individuals at risk for AD, such that positive correlations between cardiovascular fitness and hippocampus volume were observed in older adult women but not men, whereas positive correlations were observed between cardiovascular fitness and episodic memory in older adult men but not women (Dougherty et al., 2017).

### Exercise intervention with multiple exercise modalities, memory, and brain function

Current evidence has highlighted that exercise training or increased physical fitness might function as a non-pharmaceutical strategy against the deleterious effects of aging and AD on memory capacity and brain function; however, it should be noted that the majority of studies have focused on a single exercise modality (e.g., aerobic or resistance training) (Chen et al., 2020a,b). Systematic and meta-analytic reviews have revealed that exercise programs combining multiple exercise modalities (e.g., resistance training combined with aerobic exercise) might potentially evoke even greater benefits on cognitive functions (Kramer and Colcombe, 2018; Tomporowski and Pesce, 2019; Chen et al., 2020a). Notably, health-related physical fitness (e.g., cardiovascular fitness and muscular fitness) and skill-related physical fitness (e.g., balance, coordination, and power) (American College of Sports Medicine., 2018) might impact cognitive functions (Netz, 2019) and activation patterns of the frontal gyrus and premotor cortex regions (Voelcker-Rehage et al., 2010) differentially, reflecting a potential mediating role of type of fitness on cognitive function and brain regions. These results also suggest that the effects of the exercise interventions might vary according to the exercise modalities included in the program. For instance, although an exercise intervention combining aerobic and resistance exercise showed no significant effects on working memory in healthy older adults (Linde and Alfermann, 2014; Gajewski and Falkenstein, 2018), a 6-month exercise program combining multiple fitness modalities including aerobic, strength, flexibility, balance, and coordination maintained working memory performance in older women (Klusmann et al., 2010). Meanwhile, a multi-domain exercise intervention, combining aerobic and resistance exercises, balance, and flexibility training (two 1-h on-site sessions and three 20-min home-based sessions per week), showed no significant differences in episodic memory performance in a sample of older adults who suffered from subject memory complaints or objective/clinical apparent memory impairment (Fissler et al., 2017). However, a similar 6-month multi-domain exercise intervention, which consisted of aerobic, resistance, flexibility, balance, and coordination training, enhanced episodic memory in cognitively healthy older women aged 70–93 years (i.e., Mini-Mental State Examination scores ≥26) (Klusmann et al., 2010), suggesting that variations in participant characteristics might have impacted the outcomes.

In addition to the Western-style exercise, evidence has suggested that Eastern mind-body exercise (e.g., Tai Chi Chuan/Tai Ji Quan/Taiji) has cognitive benefits in older adults (Chang et al., 2010). Most Eastern mind-body exercise includes complex coordinated sequential movements and multiple forms of exercise (e.g., aerobic fitness, muscular fitness, balance, flexibility, and coordination), as well as emotional and psychosocial components (e.g., mental concentration, breathing control, and meditation) (Chang et al., 2014). Eastern mind-body exercises have been linked to stimulating multiple aspects of cognitive functioning and have been recommended for preventing age-related cognitive decline in older adults (Chang et al., 2010). For instance, improved delayed recall on an episodic memory task has been reported in older adults with MCI after a 6-month Tai Chi intervention (Sungkarat et al., 2018). Evidence from systematic and meta-analytic research has also revealed improved performance in episodic memory in older adults with MCI (Zou et al., 2019), as well as working memory and episodic memory in older adults (Ye et al., 2021), suggesting that there are benefits of mind-body exercise on various memory domains among older adults, even among those with cognitive impairment. Neuroimaging research using resting-state functional magnetic resonance imaging (rs-fMRI) has provided further evidence showing the benefits of mind-body exercise on memory (Tao et al., 2016). For instance, intervention research using high-resolution fMRI showed that the Tai Chi group had better memory performance which was correlated with increased resting-state functional connectivity (rs-FC) between the hippocampus and medial prefrontal cortex in cognitively healthy older adults (Tao et al., 2016). While evidence has suggested benefits of exercise on memory, prior interventions have not combined both Eastern and Western-style exercise using multiple modalities. At the same time, the effects of interventions on cognitive function and brain function might vary according to the exercise modalities and the characteristics of the participants examined. Accordingly, whether an integrated intervention encompassing both Western style of physical fitness training and Eastern mind-body exercise affects memory and brain function in adults at risk for dementia remains less examined and requires further investigation.

### Other modifiable lifestyle factors, memory, and brain function

Other non-pharmaceutical interventions or modifiable lifestyle factors (e.g., meditation and social interaction) have been proposed to mitigate age-related cognitive decline (Livingston et al., 2020). Meditation (e.g., mindfulness, transcendental meditation, and Vihangam yoga), a self-regulatory technique for maintaining attention and concentration on a single aspect of sensation and focusing on the present moment (Fox et al., 2014), has been considered a cognitively stimulating activity (Gallant, 2016). Research focusing on the effects of meditation-based interventions on memory has revealed promising results (Levi and Rosenstreich, 2019). Interventional-based research comparing the effects of meditation practice on operation span test performance found improved working memory in young adults (Mrazek et al., 2013). The benefits of meditation on working memory have been reported in one recent meta-analytic study of cognitively healthy and impaired older adults aged 60 years or above (Chan et al., 2019), suggesting the potential benefits of mindfulness training for improving working memory capacity in older adults. Additionally, the beneficial effects of meditation on episodic memory have been observed (Van Vugt et al., 2012; Basso et al., 2019; Nyhus et al., 2019), suggesting the potential benefits of meditation for improving episodic memory capacity.

The long-term practice of meditation has been related to changes in memory-related brain function. Increased cortical activity in the Default Mode Network (DMN) (Froeliger et al., 2012) in experienced meditators relative to non-meditators has been reported. Findings from interventional research in older adults also suggested altered connectivity within the DMN, and between the DMN and other nodes (Cotier et al., 2017). Considering the DMN has been linked to working memory (Piccoli et al., 2015) and episodic memory (Huo et al., 2018), these findings might imply superior memory in older adults who meditate. Indeed, reviews and meta-analyses indicated that extensive meditation practice was associated with changes in the frontoparietal network and higher brain efficiency during tasks involving memory (Levi and Rosenstreich, 2019).

Social interaction might also be involved in mitigating age-related cognitive decline (Evans et al., 2019; Livingston et al., 2020). Kelly et al. (2017) conducted a meta-analysis on the associations between social relationships and cognitive functions of healthy older adults by examining the effects of different social relationships (i.e., social activities, social networks, and social support) on working memory and episodic memory, showing that greater social activity and social support were associated with superior working memory and episodic memory, respectively. Evidence for the importance of social relationships has also been supported by research examining the effects of social isolation on cognitive functioning (Evans et al., 2019), and social isolation indexed by the social network index and social activity has been correlated with poor late-life memory. Finally, findings from cohort and longitudinal research (Berkman et al., 2000; Sommerlad et al., 2019), as well as systematic reviews and meta-analyses, have suggested the detrimental effects of less social engagement on risk for dementia (Penninkilampi et al., 2018; Saito et al., 2018; Sundström et al., 2020).

Collectively, while meditation and social interaction benefit memory and enhance brain function, whether meditation and social interactions in combination with multi-domain exercise positively affect neurocognition remains unknown and requires further investigation.

### The moderators and mediators of exercise, cognitive function, and brain function

Age-related cognitive decline and late-onset AD might be influenced by several risk factors, such as the apolipoprotein E (*APOE*) gene (Martins et al., 2005). *ApoE* has three common allelic isoforms (i.e., epsilon (ε)2, ε3, and ε4). Among them, the *ApoE* ε4 allele(s) has been closely associated with cognitive impairment (Martins et al., 2005; Wang et al., 2011). The *ApoE* ε4 allele(s) is overrepresented in late-onset AD, and it has been reported that more than 48% of the AD population carries one or more *ApoE* ε4 alleles (Ward et al., 2012). *ApoE* ε4 allele(s) status has also been associated with disease progression from MCI to AD, such that the onset of AD could be reported 8–16 years earlier among individuals with the *ApoE* ε4 allele(s), compared to non-*ApoE* ε4 allele carriers (Liu et al., 2013), indicating as well even faster rates of cognitive decline (Martins et al., 2005).

The *ApoE* ε4 allele(s) might also influence the effects of exercise on cognitive functioning and the risk for AD (Hamer and Chida, 2009; Wang et al., 2011). Higher physical activity levels are more strongly associated with superior memory among older adults with one or two *ApoE* ε4 allele(s) (Smith et al., 2011). Alternatively, research has suggested a positive correlation between cardiovascular fitness levels and verbal learning memory in older adults, irrespective of the status of *ApoE* ε4 allele(s) (Boots et al., 2015). Interestingly, a positive correlation between cardiovascular fitness and performance on the Rey Auditory Verbal Learning Test was only observed in older adult men at risk for AD, indicating that there might be a gender-specific effect of cardiovascular fitness on episodic memory in older adults at risk for AD (Dougherty et al., 2017). Finally, compared to sedentary older adults with the *ApoE* ε4 allele(s), older *ApoE* ε4 carriers with higher exercise levels had better performance on the Sternberg task (Deeny et al., 2008), suggesting the benefits of exercise on working memory among those with greater genetic risk for AD. Notably, while evidence suggests that the *ApoE* genotype moderates the influence of exercise and physical fitness levels on memory, no investigation thus far has examined the role of the *ApoE* genotype in an integrated intervention composed of Western-style physical fitness training and Eastern mind-body exercise.

Exercise-evoked brain-derived neurotrophic factor (BDNF) might be a candidate biological mechanism for improving cognitive function (Miranda et al., 2019; Heinze et al., 2020). BDNF, a member of the neurotrophic family with the highest levels found in hippocampal neurons (Murer et al., 2001), has been considered a putative mediating factor with multiple aspects influencing neuronal survival and maintenance (Benarroch, 2015), as well as hippocampal-related memory formation and maintenance (Bramham and Messaoudi, 2005; Miranda et al., 2019). While BDNF is the most pervasive neurotrophin in the developed adult brain (Song et al., 2015), correlations between decreased plasma BDNF concentration, increasing age (Lommatzsch et al., 2005), and poor memory performance in healthy older adults (Erickson et al., 2010) and older adults with MCI and AD dementia (Borba et al., 2016) have been observed. Research that has explored exercise training and BDNF levels in relation to the memory has revealed improved spatial memory and increased hippocampal volume following an aerobic exercise intervention, and these exercise-induced changes in hippocampal volume were correlated with elevated serum BDNF levels (Erickson et al., 2011). Meta-analytic research has further indicated that regular exercise might not only elevate resting peripheral BDNF concentrations (Szuhany et al., 2015; Dinoff et al., 2016), but also intensify BDNF responsivity immediately after both acute and regular exercise (Szuhany et al., 2015). Notably, prior studies mainly applied a single type of exercise, leaving the effects of multi-domain exercise on BDNF and memory in older adults unknown.

### Aims of the study

Several studies have examined the independent effects of chronic exercise, meditation, or social interaction on memory and brain health; however, research has yet to examine the influence of multi-domain exercise with the consideration of moderators and mediators on memory in adults at risk for AD. The current study entitled Western-Eastern Brain Fitness Integration Training (WE-BFit) Trial aims to utilize a randomized controlled design to examine the effects of a 6-month multi-domain exercise program combining multiple exercise modalities (i.e., aerobic exercise, resistance exercise, coordinative, and flexibility exercise), meditation, and social interaction on working memory and episodic memory, as well as brain function, in cognitively healthy late middle-aged and older adults. Additionally, whether the effects of this intervention will be affected by *ApoE* genotype, the status of physical fitness, or neurotrophic changes will be further examined (Figure 1).

**Figure 1 F1:**
[figure not shown]
The overall picture of the Western-Eastern Brain Fitness Integration Training (WE-BFit) Trial. *ApoE*, apolipoprotein E; BDNF, brain-derived neurotrophic factor; PF, physical fitness; exe., exercise.

## Methods

### Study design and schedule

The multi-domain interventional trial of WE-BFit is designed as a double-arm, randomized controlled trial (RCT) targeting potential factors for promoting working memory, episodic memory, and brain function in cognitively healthy late middle-aged and older adults who are and who are not at genetic risk for AD. The trial is planned to start in April 2022 and aims to recruit 100 eligible participants who will be randomly assigned into two parallel groups (i.e., the multi-domain exercise group, *n* = 50; the control group, *n* = 50). *ApoE* genotypes of eligible participants will be examined at the baseline assessment. Additionally, other primary outcomes (i.e., working memory, episodic memory, and brain function) and secondary outcomes (i.e., multiple components of physical fitness and BDNF) will be assessed before and after the 6-month intervention. This trial will be led primarily by the Faculty of Physical Education and Sport Sciences of the National Taiwan Normal University. A flow chart of the current trial is presented in Figure 2.

**Figure 2 F2:**
[figure not shown]
Study flowchart. *ApoE*, apolipoprotein E; BDNF, brain-derived neurotrophic factor; fMRI, functional magnetic resonance imaging; rs-fMRI, resting-state functional magnetic resonance imaging.

### Participants

To ensure a sufficient sample size, the sample size calculation for the current study was conducted using G^*^Power version 3.1.9.4 (ANOVA; repeated measures, within-between interaction). Multiple recruitment strategies will be utilized, including online social media advertising and word-of-mouth referrals, as well as posters and flyers placed or distributed in local community centers and organizations. Finally, individuals from previous studies will also be screened for recruiting potential participants. Before participating in the current study, potential participants will be screened by phone, followed by an on-site interview to ensure they meet the inclusion criteria.

Eligible participants (half of them are *ApoE* ε3/ε4 or *ApoE* ε4/ε4 carriers) will be provided sufficient information, and informed consent relating to the study will be provided prior to the initiation of the study. Recruitment, enrollment, and randomization will occur on a rolling basis. Finally, a total of 100 community-dwelling, cognitively healthy adults aged 45–70 years who are able to participate in moderate-intensity exercise will be recruited in a 1-year time period in Taipei, Taiwan. The inclusion and exclusion criteria are detailed in Table 1.

**Table 1 T1:** Inclusion and exclusion criteria for participating in the study.

**Inclusion criteria**	**Exclusion criteria**
- Adults aged from 45 to 70 years	- Diagnosed or self-reported cognitive problems (e.g., mild cognitive impairment or dementia)
- Normal or corrected-to-normal vision	- The diagnosed or self-reported physical disease (e.g., untreated hypertension and chronic heart disease, stroke, brain tumor, musculoskeletal disorders, other exercise contradictions)
- Able to speak and read Chinese	- Diagnosed or self-reported major psychiatric illness (e.g., major depression, schizophrenia)
- Scores of MMSE ≥ 25	- Diagnosed or self-reported neurodegenerative disease (e.g., AD and other dementias, PD and PD-related disorders, Huntington's disease)
- PAR-Q score = 0	- History of severe alcohol or drug abuse
- Able to conduct the exercise with moderate intensity	- History of chemotherapy
- Meet the criteria to undergo MRI	- Unable to complete the MRI scan
	- Traveling consecutively for 3 weeks or more during the study
	- Unwillingness to be randomized to one of the two groups
	- Currently participating in another study trial

AD, Alzheimer's disease; MMSE, Mini-Mental Status Examination; MRI, magnetic resonance imaging; PAR-Q, Physical Activity Readiness Questionnaire; PD, Parkinson's disease.

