### Assessments and outcome measures timeline

All participants will undergo multiple assessments before (Baseline-Assessments) and after (Post-Assessments) the intervention. The Baseline-Assessments will be organized into two assessment days (ADay) in the following order: (1) ADay_1_: psychosocial measures, blood extraction, and physical fitness assessment, and (2) ADay_2_: fMRI scans. The same assessment order (ADay_3_ and ADay_4_) will be carried out in the Post-Assessments. Assessments will be carried out at National Taiwan Normal University, and fMRI scans will be performed in the Imaging Center for Integrated Body, Mind, and Culture Research in National Chengchi University, Taipei, Taiwan, within 3 weeks of completion of the initial screening and the cessation of the 6-month intervention (Table 2). The timeline for the trial is visualized in Figure 3.

**Table 2 T2:** Assessments.

	**Recruitment**	**Baseline-assessments** **(**<**3 weeks before the intervention)**		**6-month intervention**			**Post-assessments** **(**<**3 weeks after the** **intervention)**	
	Screening	**ADay** _ **1** _	**ADay** _ **2** _	Initial intervention	Middle intervention	Final intervention	**ADay** _ **3** _	**ADay** _ **4** _
Information of study	**X**							
Review of criteria	**X**							
Medical history, General health status, MMSE, PAR-Q	**X**							
Informed consent form	**X**							
Battery of psychosocial measures	**X**						**X**	
Blood extraction		**X**					**X**	
Battery of physical fitness tests		**X**					**X**	
Magnetic resonance imaging			**X**					**X**
rs-fMRI								
fMRI: n-back task, RISE task								
Attendance				**X**	**X**	**X**		

ADay, Assessment days; MMSE, Mini-Mental Status Examination; PAR-Q, Physical Activity Readiness Questionnaire; rs-fMRI, resting-state functional magnetic resonance imaging; RISE, relational and item-specific encoding.

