#### Functional magnetic resonance imaging acquisition and analysis

All participants will undergo a series of whole-brain functional magnetic resonance imaging (fMRI) before and after the intervention. The data acquired will include resting-state fMRI (rs-fMRI) and task-evoked fMRI using a Siemens 3.0 T MRI scanner (Magnetron Prisma, Siemens, Germany) with a 32-channel head coil at the Imaging Center for Integrated Body, Mind, and Culture Research in National Chengchi University, Taipei, Taiwan. The parameters for MRI screening will be adapted from previous studies (Castells-Sánchez et al., 2019; Erickson et al., 2019).

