#### Genotype and blood assays

##### *ApoE* genotype

Blood samples from the antecubital veins will be collected by licensed medical technicians/nurses during participants' first visit to the laboratory before the random assignment. The genotypes will be determined using a polymerase chain reaction method with modification. Two (rs429358: *ApoE* C112R; rs7412: *ApoE* R158C) genes will determine identification of the *ApoE* allele(s) (*ApoE* ε2, *ApoE* ε3, and *ApoE* ε4). Based on the genotypes, participants will be categorized as high risk (*ApoE* ε3/ε4 and *ApoE* ε4/ε4) or low risk (*ApoE* ε2/ε2, *ApoE* ε2/ε3, *ApoE* ε2/ε4, and *ApoE* ε3/ε3) for AD occurrence.

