### Power analysis

The study will recruit a total sample size of 100 participants for final statistical analyses. The sample size is estimated from an *a priori* power analysis using G^*^Power 3.1.9.4 (power = 0.80, alpha = 0.05) and the effect size (Hedges' *g* = 0.30) based upon our previous meta-analysis that examines the effects of exercise interventions on executive function, including working memory in adults of age 55–65 years (Chen et al., 2020a).

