Several challenges of this study are worth mentioning. For instance, the current trial will recruit 50 cognitively healthy participants with a genetic risk for AD. Nevertheless, the recruitment of sufficient participants is challenging, given that the prevalence of *ApoE* ε4 allele(s) in Taiwan is only around 20% (Hong et al., 1996; Wang et al., 2011). Unfortunately, this challenge will be further escalated by the occurrence of the COVID-19 pandemic. Although this challenge might be partially alleviated through recruiting *ApoE* ε4 allele(s) carriers from our previous research and the progressive ease of the COVID-19 pandemic in Taiwan, we still expect the inclusion of a sufficient number of participants, especially the *ApoE* ε4 allele(s) carriers, will be difficult. Drop-out and adherence will be other challenges in the current study. Two strategies will be applied to curtail these challenges. First, frequent contacts and regular newsletters will be delivered to all participants from the research group. Furthermore, the multi-domain exercise group can attend two out of 10 optional exercise sessions each week instead of adhering to a fixed exercise schedule. These approaches enhance the personal connection to the study and provide user-friendly access to the exercise program, and we expect this to enhance participants' adherence and minimize the risk of them withdrawing from the intervention (Robiner, 2005). Finally, the current trial collects a considerable amount of outcome measures, and many of them have to be collected in a time-sensitive manner. For instance, to accurately reflect the relationships between physiological conditions and brain health, physical fitness, BDNF levels, cognitive tasks, and fMRI assessments will be completed within 3 weeks before and after the 6-month exercise program, respectively. To overcome this potential challenge, a limited number of participants (e.g., five people) will be grouped as one intervention unit, and the unit will coordinate the most suitable time for initiating the assessments and exercise program.

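### The same 100 is given as the number randomised and the number analysed although drop-out is expected, and the two-wave ANOVA in its standard form uses only participants with both assessments

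*Protocol article*

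**What the plan says.** **Numbers.** Study design and schedule: the trial "aims to recruit 100 eligible participants who will be randomly assigned into two parallel groups", 50 in each. Power analysis: "The study will recruit a total sample size of 100 participants for final statistical analyses". That section gives power 0.80, alpha 0.05 and Hedges' g = 0.30. The Participants section names the G*Power procedure for the within-between interaction. No loss rate or inflation is given.

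**Expected loss.** Discussion: "Drop-out and adherence will be other challenges in the current study". Frequent contact and flexible sessions are offered as countermeasures.

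**Analysis.** Statistical analysis: each primary outcome has its own mixed-design ANOVA, with group between subjects and the baseline and post assessments within subjects.

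**Criteria.** Table 1 lists among the exclusions "Traveling consecutively for 3 weeks or more during the study" and "Unable to complete the MRI scan". Table 2 marks the row "Review of criteria" at screening only. On imaging: "All participants will undergo a series of whole-brain functional magnetic resonance imaging (fMRI) before and after the intervention". Blood for genotyping is taken "during participants' first visit to the laboratory before the random assignment". The text does not say whether the baseline scan day falls before or after allocation.

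**The concern.** One figure does two jobs. If 100 are randomised and some are lost, fewer than 100 are analysed. If 100 must be analysed, more must be randomised. The reader cannot tell which the power calculation supports.

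The stated analysis makes the gap matter. A two-wave repeated-measures ANOVA is equivalent to comparing change scores between arms, and a person with only a baseline has no change score. The n-back and RISE tasks are performed during the scans, so a missed post-intervention scan day can remove the memory outcomes as well as the imaging. What remains is a comparison of people who came back, and it matches the randomised comparison only if loss is unrelated to baseline and outcome.

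At stake are a modest amount of power, some precision that the ANOVA gives up even without loss, and protection against loss that depends on baseline.

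**Working it through.** **Inputs.** From the article: 100 participants, 1:1, power 0.80, alpha 0.05, g = 0.30, two groups, two time points. Assumed because not stated: conversion f = g/2 = 0.15; correlation rho = 0.5 between waves; loss of 10% to 20%.

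**1. The plan's own figure.** For the within-between interaction, the noncentrality is lambda = N × m × f² / (1 − rho), with m = 2 and degrees of freedom 1 and N − 2. With f = 0.15 and rho = 0.5, lambda = N × 2 × 0.0225 / 0.5 = 0.09N. The smallest even N with power of at least 0.80 is 90 (lambda = 8.1, power 0.804), not 100. A figure near 100 can be reached in two ways, each needing an input the article does not give:
- rho = 0.45 gives N = 98.
- N = 90 with a 10% allowance gives 90 / 0.90 = 100.

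**2. Power if 100 are randomised and only two-wave participants count** (f = 0.15, rho = 0.5):

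| Loss | Analysed N | lambda | Power |
|---|---|---|---|
| 0% | 100 | 9.00 | 0.844 |
| 10% | 90 | 8.10 | 0.804 |
| 20% | 80 | 7.20 | 0.755 |

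The result depends on rho. At rho = 0.45 the three values are 0.808, 0.765 and 0.715. At rho = 0.6 they are 0.913, 0.882 and 0.842.

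**3. Number to randomise if 100 must be analysed.** 100 / 0.90 = 111.1, so 112 at 10% loss. 100 / 0.80 = 125 at 20%, or 126 for equal arms.

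**4. What the ANOVA gives up in precision.** With unit variance at each wave, the change score has variance 2(1 − rho) = 1.00 at rho = 0.5. The baseline-adjusted outcome has variance 1 − rho² = 0.75. The ratio is 0.75, a 25% reduction in the variance of the contrast.

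**5. Loss that depends on baseline.** Suppose there is no true effect, 20% of the exercise arm is lost, and a normally distributed tendency to leave correlates 0.5 with low baseline.
- The 80% who remain have a baseline mean shifted by 0.5 × 0.280 / 0.80 = 0.175 SD, where 0.280 is the normal density at the 80th percentile.
- Change falls by 1 − rho = 0.5 per unit of baseline, so the change-score contrast is biased by 0.5 × 0.175 = 0.09 SD. Here the bias goes against exercise; it reverses if people with high baselines leave.
- A large-sample simulation gave a bias of 0.09 SD in size for the change-score contrast and 0.00 for the baseline-adjusted one.

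**6. Loss that depends on the unobserved outcome.** Repeat step 5 with leaving correlated 0.5 with poor change. The change-score contrast is biased by about 0.18 SD and the baseline-adjusted contrast by about 0.13 SD. Adjustment does not remove this bias. Only post-assessments from those who stop would address it.

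**The case against.** The strongest reply is that analysis sets and missing-data handling commonly sit in a full protocol or analysis plan, which is not shown, and that the article never states listwise deletion. That stands: the absence of such a paragraph is not counted here. But the article does name the model for every primary outcome and does give 100 as the analysed number. Those are stated choices.

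A second reply is that 100 may already hold a 10% allowance over 90. The arithmetic allows it, but the Power analysis section assigns the 100 to the final analyses, so the allowance cannot be credited as written.

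Three stronger readings are tempting and are not supported.

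- **That the plan removes randomised people who travel or miss a scan.** The travel wording covers the whole study and the MRI wording has no time point, so a reader might infer this. But both sit in a table of entry criteria, the criteria are reviewed at screening, and nothing in the article removes anyone after allocation. It is an ambiguity, not a rule.
- **That completers overstate the benefit by 25%.** This would follow if 20% of the exercise arm left with no gain while completers gained 0.30 SD (0.30 against 0.8 × 0.30 = 0.24). The documents give no such rate or mechanism, nor any basis for fixing the direction of bias. The proposed model would not correct such loss by itself either.
- **That drop-out brings power down to 0.26–0.29.** Those values read g = 0.30 as a difference in change (f = 0.075). On that reading power is already 0.318 with no loss, then 0.291 at 45 and 0.263 at 40 per arm. Loss accounts for only about 0.03 to 0.05. The rest is a separate question about converting the effect size.

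**Conclusion.** The point holds in a limited form. The randomised and analysed numbers agree only with zero loss, which the article itself does not expect. The stated ANOVA, in its standard form, discards anyone with one wave.

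The power cost is small: from 0.844 to 0.804 at 10% loss and 0.755 at 20%, given f = 0.15 and rho = 0.5. The case for changing the model rests more on about 25% lower variance at that correlation and on protection against baseline-dependent loss, where the illustration gave a bias of about 0.09 SD. The correlation, the conversion of g to f, the loss rates and the loss mechanism are all assumptions. The timing of the two exclusion criteria is a minor matter of wording.

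**What to change.** 1. State that 100 is the number randomised. Add an assumed loss rate, the expected analysed number and its power, with the correlation and the conversion of g to f. If 100 analysed is really intended, raise the number randomised accordingly.
2. Replace the group-by-time ANOVA with a likelihood-based mixed model that constrains the baseline means to be equal across arms, fitted to all randomised participants in their assigned arm.
3. Invite everyone randomised to the post-assessment, including those who stop attending sessions. The model alone does not correct loss that depends on the unobserved outcome.
4. In Table 1, say that the travel and MRI criteria are judged before randomisation only, for example as travel already planned at screening and the baseline scan. State that allocation follows the baseline scan if that is so.

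Items 1, 2 and 4 cost wording and a model that is easily fitted. Item 3 costs some staff time, scanner time and reimbursement. The estimate will include people who did not adhere and may be somewhat smaller.
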